### Index tests

The index tests of VERDICT MRI and LWI will be performed on a 3T MRI scanner (Achieva or Ingenia, Philips Healthcare, Best, Netherlands). Sequence parameters are detailed in tables 1 and 2. These will be additional to the clinical multiparametric sequence. Total scan time will be a maximum of 1 hour.

**Table 1 T1:** Sequence parameters for Verdict MRI

Verdict MRI		
**MR scanner**	**Achieva (3T**)	**Ingenia (3T**)
Receive coil (s)	32 channel Cardiac coil	Body coils
Sequence	DWI SE EPI single shot	DWI SE EPI single shot
Field of view (mm)	220	220
No of slices	14	14
Slice thickness (mm)	5	5
Slice gap (mm)	0	0
phase encoding direction	AP	AP
Reconstructed matrix	176×176	176×176
Reconstructed pixel size (mm)	1.25	1.25
**b-values**	0.3000	0.3000
Repetition time (TR) range, actual (ms)	3349–10 000,2260	3349–10 000, 6292
Echo time (TE) (ms)	80	87
Water fat shift WFS(pix)/Bandwidth(Hz)	49.09/8.8	57.54/7.5
DELTA/delta (ms)	38.8/18.9	43.4/20.0
No of signal averages	6	6
**b-values**	0.2000	0.2000
TR range, actual (ms)	2000–10000, 3897	2000–10000, 6699
TE(ms)	67	75
WFS(pix)/BW(Hz)	49.09/8.8	57.55,7.5
DELTA/delta (ms)	32.3/12.4	37.4, 14.0
Number of signal averages	6	6
**b-values**	0.1500	0.1500
TR range, actual (ms)	2000–10000, 2398	2000–10000, 2967
TE(ms)	90	94
WFS(pix)/BW(Hz)	49.09/8.8	58.05, 7.5
DELTA/delta (ms)	43.8/23.9	46.9, 23.3
Number of signal averages	6	6
**b-values**	0.500	0.500
TR range, actual (ms)	2482–10000, 2482	2000–10000, 2229
TE(ms)	65	68
WFS(pix)/BW(Hz)	49.06/8.8	58.05, 7.5
DELTA/delta (ms)	31.3, 11.4	33.9, 10.3
Number of signal averages	6	6
**b-values**	0.90	0.90
TR range, actual (ms)	2482–10000, 2482	2000–10000, 2024
TE (ms)	50	54
WFS(pix)/BW(Hz)	49.09,8.8	57.54, 7.5
DELTA/delta (ms)	23.8/3.9	26.9, 3.5
No of signal averages	4	4
Acquisition time (minute: second)	10:95	17:41

DWI SE EPI, Diffusion Weighted Imaging Spin Echo Echo Planar Imaging.

**Table 2 T2:** Sequence parameters for Luminal Index Imaging MRI

Luminal index imaging		
**MR scanner**	**Achieva**	**Ingenia**
Receive coil (s)	32 channel Cardiac coil	Body Coils
**Sequence**	TSE (multishot)	FSE
**FOV (mm**)	180	180
N of slices	19	19
**Slice thickness (mm**)	3.5	3.5
**Slice gap (mm**)	0.35	0.35
Phase encoding direction	Right Left	Right Left
Reconstructed matrix (read)	224×224	224×224
Reconstructed pixel size (mm x mm)	0.94×0.94	0.94×0.94
Echo times (ms)	31.25/62.5/93.8/125/156.3/187.5/218.8/250	31.25/62.5/93.8/125/156.3/187.5/218.8/250
Repetition time (ms)	Shortest (7676 ms)	Shortest (7676 ms)
No of echoes	8	8
Receive bandwidth	WFS 2.99 / (144.8.6 Hz/px)	WFS 2.99 / (144.8.6 Hz/px)
No of signal averages	1	1
Turbo factor	8	8
Acquisition time (minute: second)	06:44	05:39

FSE, Fast Spin Echo; TSE, Turbo Spin Echo; WFS, water fat shift.

The VERDICT MRI technique has been described in previous publications^11^; a summary is given below. VERDICT uses a pulse-gradient spin-echo sequence acquired with a 32-channel cardiac coil with b values of 90–3000 s/mm^2^ in 3 orthogonal directions. For b=90 s/mm^2^, the number of signal averages (NSA) was 4 and for other b values, the NSA was 6. The voxel size is 1.3×1.3×5 mm, matrix size=176×176. A b=0 s/mm^2^ image for every echo time (TE) is acquired to mitigate T2 dependence. After processing, estimates of intracellular volume fraction (FIC), extravascular extracellular volume fraction (EES), vascular volume fraction (FVASC) are generated by a previously described method.^17^

LWI comprises of a multiecho spinecho sequence with an echo spacing of 31.25 ms and repetition time (TR) of 8956 msec. The field of view (FOV) is 180×180 mm and acquired voxel size=0.9×0.9×3.5 mm with a scan duration of 5 min 50 s. LWF values for lesions identified on mpMRI will be calculated after data processing by a previously described method.^7^

### Data analysis

Reporting of clinical mpMRI will follow standard of care and be reported by Uro-radiologists based at UCLH on an ordinal Likert scale (1–5): 1—tumour highly unlikely, 2—tumour unlikely, 3—equivocal, 4—tumour likely and 5—tumour highly likely. If the mpMRI study is reported as Likert three or four and the patient is offered a biopsy, a radiologist (blinded to biopsy results/histopathology) will use the pictorial report to derive index test quantitative parameters: FIC for VERDICT MRI and LWF from LWI. Thresholds of index test parameters based on previous work from the INNOVATE trial will be applied to determine whether a lesion is positive or negative.^7^ This will be compared with a histological reference standard allowing assessment of false positive rate, sensitivity and specificity.

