**Figure 1 F1:**
[figure not shown]
Protocol for matching MRI to Whole mount histology. The participant’s prostate is contoured by a radiologist on preoperative imaging (‘in vivo MRI’) slice by slice. Based on these contours, a mould specific to the participant’s prostate is 3D printed. The ‘reference slice’ is predefined based on the location of the tumour. After prostatectomy, the prostate is scanned in the mould (‘ex-vivo MRI’). The prostate is sectioned first at the predefined reference slice. The remainder of the prostate is then sliced as standard. Stained ‘whole Mount histology’ is then matched with ex vivo and in vivo imaging. 3D, three dimensions.

The primary objective is to assess whether the index tests can reduce false positives from mpMRI by 20% for men undergoing biopsy or biopsy and prostatectomy. Clinically significant prostate cancer (csPCa) for biopsies is defined as any single biopsy core containing Gleason grade 3+4 or above. For prostatectomy, csPCa is defined as the predominant grade of 3+4 or above in the same matched region on whole mount histology as the abnormality on MRI.

The secondary objectives will examine the proportions of true positive lesions from the index tests.

Exploratory analyses will determine the correlation of VERDICT and LWI parameters to histological parameters. For VERDCIT MRI: fractional intracellular fraction (FIC) to fractional histological intracellular component, fractional extracellular extravascular space to histological glandular and stromal component and fractional vascular volume (FVASC) to histological vascular component. For LWI, luminal water fraction (LWF) will be correlated to luminal space fraction.

Matched MR and histology images will be used as training data for machine learning algorithms. The algorithms will be used to solve a variety of regression problems where the input is MRI and the output is the histological features in each voxel or the full histological image appearance itself, building on previous work from our group.^14–16^

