### Statistical analyses

A sample size of 128 subjects achieves a 90% power to detect a difference of 20% in the proportion of false positives between the index tests (0.45) and standard test (0.65). This calculation uses a two-sided Pearson χ^2^ test with a significance level of 0.05 and confidence level of 95%. We anticipate a biopsy rate of 57% in the cohort and of those biopsied, 75% to be scored Likert 3 or 4, based on results from the recent INNOVATE trial at our institution.^7^ Therefore, a sample size of 300 will provide sufficient power, with an estimated 171 men predicted to have biopsy and of these men, 128 to have a Likert score of 3 or 4.

Approximately 800 patients undergo prostatectomy per year at UCLH and 150 are referred from Barts Health National Health Service(NHS) trust. We estimate in a sample size of 300, approximately 50 patients will elect to have a prostatectomy based on clinical experience and recruitment in other studies carried out at our institution.

The difference in proportion of false positives and true positives for the index test will be compared with the standard test (mpMRI) using a χ^2^ test. Correlation coefficients will be used to determine the correlation between index test parameters and histological measures.

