## Discussion

Histology remains the gold standard of prostate cancer diagnosis and therefore represents the best reference standard for novel MRI techniques. This observational study aims to test the predictive capabilities of novel MRI techniques without compromising on standard clinical care. Furthermore, matched MRI and histological data will provide a rich data set for training machine learning algorithms.

This study design has some limitations. Biopsy decisions will not be influenced by the index tests therefore we cannot determine their true sensitivity and specificity. However, at this stage of biomarker development, prospective validation of thresholds derived from a previous study is required before biopsy decisions could be determined by the index tests.^7^ Given the high negative predictive value of mpMRI,^18 19^ it would also lead to unnecessary morbidity if patients with negative mpMRI are biopsied. The inherent sampling error with biopsies is also a limitation of this study in men who do not undergo prostatectomy. However, if only men undergoing prostatectomy were selected in this study, histological validation will be limited by spectrum bias where more aggressive tumours are selected.

The results of this study may not be generalisable to other centres. The two index tests have been optimised on scanners from the same vendor. Formal reproducibility studies are required to assess whether the index tests perform as well on different systems before multicentre trials can be performed.^20^

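### The primary comparison is one-directional on the denominator that the sample size implies, and primary success carries no condition on clinically significant cancers retained

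*Protocol article*

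**What the plan says.** All references are to the protocol article.

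- **Study Design, after Figure 1:** "The primary objective is to assess whether the index tests can reduce false positives from mpMRI by 20% for men undergoing biopsy". Men who go on to prostatectomy are included. True-positive lesions are a secondary objective. No margin is given, and primary success does not depend on them.
- **Data analysis:** "If the mpMRI study is reported as Likert three or four and the patient is offered a biopsy, a radiologist" blinded to histology derives the index parameters. Then: "Thresholds of index test parameters based on previous work from the INNOVATE trial will be applied to determine whether a lesion is positive or negative". Comparison with histology is described as "allowing assessment of false positive rate, sensitivity and specificity".
- **Index tests:** "LWF values for lesions identified on mpMRI will be calculated" after processing, so the reading is confined to what mpMRI has already marked.
- **Statistical analyses:** 128 subjects give 90% power for a 20-point difference in the proportion of false positives "between the index tests (0.45) and standard test (0.65"), using a two-sided Pearson chi-square at 0.05. Recruiting 300 men is expected to give 171 biopsied, of whom 128 score Likert 3 or 4. False positives and true positives are each compared with mpMRI by chi-square.
- **Introduction:** the clinical need is to cut false positives in Likert 3 and 4 men while not missing those with csPCa.
- **Discussion:** because the index tests do not influence biopsy, "we cannot determine their true sensitivity and specificity".

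**The concern.** Every man in the primary comparison is mpMRI-positive by selection. Within this set mpMRI has sensitivity 1 and specificity 0, and 0.65 is simply the share of men without csPCa. The index test can only confirm a positive call or reverse it. If both tests are counted over the same men, the index false-positive count cannot exceed that of mpMRI, and any reversal of a benign lesion counts as progress whether or not the marker carries information.

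The usual protection is a matching requirement on cancers kept. The primary objective has none, although the Introduction's statement of need includes it. A significant primary result would therefore not, by itself, separate a discriminating marker from one that calls lesions negative at random.

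**Working it through.** **Inputs.** False-positive proportions 0.65 and 0.45, 128 subjects, 90% power, two-sided 0.05, biopsy rate 57% and Likert 3 or 4 share 75% (all from Statistical analyses). csPCa prevalence in the analysed men is 1 − 0.65 = 0.35. Assumptions: one lesion per man, and a range for the share of lesions that the index test calls negative.

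**1. The plan's own figure.** The two-proportion formula for 0.65 against 0.45 (90% power, two-sided 0.05, no continuity correction) gives 128 per group, with power 0.900. With 64 per group the power would be 0.63. Recruitment gives 300 × 0.57 = 171 and 171 × 0.75 = 128 men in total. So 128 yields 90% power only if the same 128 men are the denominator for both tests.

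**2. What the figures mean on that denominator.** Men without csPCa: 0.65 × 128 = 83.2. Men with csPCa: 0.35 × 128 = 44.8. The planned index false positives are 0.45 × 128 = 57.6, so the implied specificity is (83.2 − 57.6)/83.2 = 0.31.

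**3. How many reversals reach significance.** With 83 mpMRI false positives and 67 index false positives, the pooled proportion is 150/256 = 0.586. The standard error is √(0.586 × 0.414 × 2/128) = 0.0616, and z = (16/128)/0.0616 = 2.03. With 68 index false positives, z = 1.91. About 16 reversals among 83 benign men are enough, whatever happens to the cancers.

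**4. A test unrelated to histology.** If it calls a share *c* of lesions negative, the expected index false-positive proportion is 0.65 × (1 − *c*). This equals 0.45 at *c* = 0.20/0.65 = 0.308. Expected csPCa cases lost are 44.8 × *c*. Results of 200,000 simulated trials of 128 men:

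| Lesions called negative | Expected false positives /128 | Planned chi-square significant | csPCa lost (of 44.8) | Secondary true-positive test significant |
|---|---|---|---|---|
| 10% | 0.585 | 1% | 4.5 | <0.1% |
| 15% | 0.552 | 19% | 6.7 | 0.3% |
| 20% | 0.520 | 61% | 9.0 | 3% |
| 25% | 0.488 | 90% | 11.2 | 16% |
| 31% | 0.450 | 99% | 13.8 | about 44% |

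The last row exceeds the planned 90% because the two counts come from the same men. The difference is the share of benign men reversed, with standard deviation √(0.20 × 0.80/128) = 0.035, less than the 0.062 that the chi-square assumes. In no simulated trial did index false positives exceed those of mpMRI.

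If success also required an observed reduction of at least 20 points, the uninformative test would succeed in about 13% of trials at 25% called negative and 50% at 31%.

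**5. The other denominator.** If 0.45 means false positives among index-positives (1 − PPV) and all 45 cancers are kept, there are 45/0.55 = 82 index-positives, of whom 37 are false positives. Specificity is then 1 − 37/83 = 0.55 to 0.56. An uninformative test stays at 0.65 on average on this reading, and a significant reduction occurred in under 0.1% of simulations. But 82 is not 128.

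**The case against.** **The population is deliberate.** Re-sorting mpMRI-positive men is the intended use, and the Discussion explains why mpMRI-negative men are not biopsied. This stands: the selection is not the flaw. The flaw is a success criterion that ignores what the selection does to the comparison.

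**Would a worthless test necessarily succeed?** A reader might infer so, but the documents do not support it. The outcome depends on how many lesions are called negative. At 10% the planned test passes about 1% of the time. The thresholds are carried over from an earlier trial, and neither their values nor their expected negative rate is given. It also depends on the denominator: on the 1 − PPV reading the problem vanishes. The Introduction's false-positive rates of 85% and 40% among biopsied men fit either reading, since for mpMRI the two coincide here. Only the sample size separates them, and it favours the 128-man denominator.

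**Are missed cancers hidden?** No. True positives are compared as a secondary objective, and Data analysis promises sensitivity and specificity, so an uninformative marker would show sensitivity close to 1 − specificity. What remains is that these outputs do not bear on primary success and that the secondary test is weak, missing a 31% loss of csPCa in more than half of trials.

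**Do Data analysis and the Discussion contradict each other?** This is tempting but weak. Data analysis speaks of Likert 3 or 4 men offered biopsy, so its measures are conditional in context, while the Discussion disclaims the true values. A label is enough.

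**Conclusion.** The point holds in a conditional form. On the denominator that reproduces 128, the primary comparison can move in only one direction and has no condition on csPCa retained. A test unrelated to histology then passes the planned chi-square in about 1% to 99% of trials as the share of lesions called negative goes from 10% to 31%. At 31%, the rate that reproduces the planned 0.45, about 14 of 45 csPCa cases are lost.

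This rests on 35% prevalence, one lesion per man, significance as the success criterion, and negative rates that are assumed because the article does not give them. It does not show that VERDICT or LWI is uninformative, or that the trial will mislead. It shows that the primary result as defined cannot establish discrimination, and that the denominator of the false-positive proportion needs to be stated.

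**What to change.** 1. **State the denominators.** Define index specificity among biopsied Likert 3 or 4 men without csPCa (about 83) and sensitivity among those with csPCa (about 45). Label both as conditional on being mpMRI-positive and biopsied. Keep the sensitivity and specificity wording in Data analysis, with that label added.
2. **Add discrimination to primary success.** Claim success only if the false-positive reduction is met and the index test beats chance, with the lower 95% limit of sensitivity + specificity − 1 above 0.
3. **Report sensitivity with its 95% confidence interval** alongside the primary result.

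**Cost.** The data are unchanged and the criterion is somewhat harder. Comparing index-positive rates in 45 against 83 men, the beat-chance part has about 98% power at sensitivity 0.95 and specificity 0.31, and 81% at 0.90 and 0.31. An uninformative test passes it about 2.4% of the time.

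Any further minimum for sensitivity is for the sponsor to choose, and 45 csPCa cases support only a loose one. If the exact lower 95% limit of sensitivity also had to exceed 0.80, joint power with the beat-chance condition would be about 81% at true sensitivity 0.95 and 33% at 0.90. For a bound of 0.85 it would be about 33% and 5%.

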### Reference standard

The reference standard for those men who undergo biopsy and/or prostatectomy will be histopathological diagnosis (figure 2). Abnormal regions identified by clinical mpMRI will be targeted at biopsy. Men who elect to have prostatectomy after positive biopsy will be processed by a published specimen handling protocol developed at our institution.^13^ Histology from biopsy and prostatectomy specimens will be assessed by two histopathologists blinded to MRI findings. Gleason grade for targeted biopsy and matched prostatectomy whole block section will be analysed and ascribed a Gleason score on consensus. Assessors of the reference standard will be blinded to MRI results. If there is a disagreement in histological assessment for a participant who undergoes both targeted biopsy and prostatectomy, the prostatectomy lesion grading will supersede.

**Figure 2 F2:**
[figure not shown]
Reference standard flow chart reference standard derived from multiparametric MRI (mpMRI) and histology for index tests. Histology refers to either a positive biopsy core in a targeted lesion or positive lesion on matched MRI and whole mount histology from prostatectomy. Histology from prostatectomy supersedes targeted biopsy.

For patients who undergo prostatectomy, in order to match MRI slices to histopathology, a patient-specific specimen handling protocol is to be used^13^ (figure 1). This protocol is needed because in standard histological processing there are changes in orientation after cutting and sampling which are difficult to account for when matching standard whole mount histology to MRI (figure 1). We create a personalised three-dimension printed mould for men undergoing prostatectomy using their preoperative MRI images (T2W imaging) in order to allow for predictable sectioning.

After surgical removal of the prostate the specimen will be positioned in the mould and scanned in a 3T MRI scanner. This will facilitate the matching between preoperative MRI and histology.

The mould defines a reference slice which has two cutting planes spaced 5 mm apart. A twin bladed knife is used to cut a 5 mm slice predefined from the mould. The rest of the prostate is then sliced at 5 mm thickness as per standard laboratory protocol. Whole mount sections are then processed for H&E staining. Additional immunohistochemical staining for vascular and stromal structures will be performed to aide in mapping with the index tests.

The matched whole mount histology slice will be assessed and used to determine whether an MRI lesion was positive (≥Gleason 3+4) or negative (≤Gleason 3+3 or negative).

### Statistical analyses

A sample size of 128 subjects achieves a 90% power to detect a difference of 20% in the proportion of false positives between the index tests (0.45) and standard test (0.65). This calculation uses a two-sided Pearson χ^2^ test with a significance level of 0.05 and confidence level of 95%. We anticipate a biopsy rate of 57% in the cohort and of those biopsied, 75% to be scored Likert 3 or 4, based on results from the recent INNOVATE trial at our institution.^7^ Therefore, a sample size of 300 will provide sufficient power, with an estimated 171 men predicted to have biopsy and of these men, 128 to have a Likert score of 3 or 4.

Approximately 800 patients undergo prostatectomy per year at UCLH and 150 are referred from Barts Health National Health Service(NHS) trust. We estimate in a sample size of 300, approximately 50 patients will elect to have a prostatectomy based on clinical experience and recruitment in other studies carried out at our institution.

The difference in proportion of false positives and true positives for the index test will be compared with the standard test (mpMRI) using a χ^2^ test. Correlation coefficients will be used to determine the correlation between index test parameters and histological measures.

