## Methods and analysis

### Study Design

Histo-MRI is an observational, prospective, cohort study recruiting men with clinical suspicion of prostate cancer from two centres: University College London Hospital (UCLH) and Barts Health. The index tests (VERDICT MRI and LWI) and standard of care mpMRI will be performed at one centralised centre (UCLH). The study opened for recruitment in October 2020 and the anticipated study end date is October 2023. Participants will undergo the both tests before undergoing biopsy if indicated by the standard test. The index tests will not be used to select patients for biopsy. If a recruited participant is diagnosed with prostate cancer and chooses to undergo prostatectomy, the prostate specimen will undergo a specific specimen handling protocol designed to align histopathology to MRI (figure 1).

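### The primary comparison is sized and tested as two independent groups of 128, but the same 128 men supply both results, so the stated 90% is not this design's power and the standard error is too large

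*Protocol article*

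**What the plan says.** All places are in the protocol article, under Methods and analysis.

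- **Study Design:** "Participants will undergo the both tests before undergoing biopsy if indicated by the standard test". Each man has mpMRI and the index tests.
- **Data analysis:** the index parameters are derived under a condition, "If the mpMRI study is reported as Likert three or four and the patient is offered a biopsy", and the radiologist "will use the pictorial report to derive index test quantitative parameters". A threshold then makes the lesion positive or negative, and the call is judged against histology.
- **Statistical analyses, sizing:** "A sample size of 128 subjects achieves a 90% power to detect a difference of 20% in the proportion of false positives". The assumed values are 0.65 for mpMRI and 0.45 for an index test. The method is named: "This calculation uses a two-sided Pearson χ^2^ test with a significance level of 0.05".
- **Statistical analyses, numbers:** 300 recruited, 57% biopsied (171), and 75% of those Likert 3 or 4 (128).
- **Statistical analyses, analysis:** "false positives and true positives for the index test will be compared with the standard test (mpMRI) using a χ^2^ test". The article names no paired method and states no agreement or discordance between the two tests.

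**The concern.** A Pearson chi-square on two proportions assumes that they come from different people. Here one man gives both results, against one histology reading. The dependence is also strong. The index test is applied only to men already called positive by mpMRI, so it can remove an mpMRI false positive but cannot add one.

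Two things follow. The power quoted for the primary objective belongs to another design, so a reader cannot tell what the 128 men can show. The standard error behind the planned test is also that of independent samples. With positively related results it is too large, so real differences of moderate size can be reported as non-significant. That matters in both directions that the Introduction cares about: fewer false positives, and no cancers missed in exchange. The secondary comparison of true positives uses the same test.

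**Working it through.** **Inputs.** From Statistical analyses: p1 = 0.65, p2 = 0.45, two-sided alpha 0.05 (z = 1.960), power 0.90 (z = 1.282), n = 128. Assumption, because the article does not define the denominator: false positives are counted over all 128 Likert 3/4 biopsied men for both tests. Expected counts are then 0.65 × 128 ≈ 83 mpMRI false positives and 128 − 83 = 45 men with significant cancer.

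**1. Reproduce the plan's figure.** The two-sample Pearson formula, with pooled p = 0.55, is

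n per group = [1.960·√(2·0.55·0.45) + 1.282·√(0.65·0.35 + 0.45·0.55)]² / 0.20² = 127.94, so 128.

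This matches, but as 128 in each of two groups, or 256 people. With 128 as the total (64 per group) the same formula gives 62.6% power. The article's own chain, 300 × 0.57 × 0.75 = 128.25, gives 128 men altogether.

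**2. Standard error at the 20-point target.**
- Unpaired: √[(0.2275 + 0.2475)/128] = 0.0609, 95% half-width 11.9 points.
- Paired and nested (20% cleared, none added): √[0.20·0.80/128] = 0.0354, half-width 6.9 points.

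The ratio is about 1.7.

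**3. Power of the planned unpaired test on nested data** (128 men, simulated):
- true 20-point cut: about 99%
- true 10-point cut: about 22%

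**4. What it takes to reach p<0.05.** Starting from 83 of 128:
- 15 cleared (83 v 68): z = 1.906, p = 0.057
- 16 cleared (83 v 67): z = 2.030, p = 0.042

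A fall of 15/128 = 11.7 points, all in one direction, would be reported as non-significant.

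**5. The same test on true positives.** If the index test keeps 31 of 45 cancers, the planned layout is 45 v 31 of 128. Pooled p = 76/256 = 0.297 and z = 14/√(256·0.297·0.703) = 1.915, so p = 0.055. Losing 14 of 45 cancers (31%) would be labelled no significant difference.

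**6. Dependence on the agreement between tests.** If nesting is set aside and P(both false positive) is varied, the power of a paired (McNemar) test at 128 men is:

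| P(both FP) | Power |
|---|---|
| 0.45 (nested) | >99.9% |
| 0.40 | 99.0% |
| 0.35 | 95.6% |
| 0.2925 (independent) | 89.3% |
| 0.20 (negative correlation) | 77.8% |

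The Data analysis section implies the first row.

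**7. Is McNemar's test enough?** No. Because the index test cannot add positives, one discordant cell is zero by construction, and six cleared false positives give exact p = 2 × 0.5⁶ = 0.031. Suppose an index test clears 15% of lesions at random, whatever the histology. The expected cleared false positives are 0.65 × 0.15 = 9.75% of 128 men, and the chance of six or more is about 99%. A useless test would reject the null almost every time.

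**8. What the data can estimate well.** At the planned effect, the share of mpMRI false positives removed is 0.20/0.65 = 31%. With 26 of 83 removed, the exact 95% CI is 22% to 42%.

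**The case against.** The strongest reply is that the error does no harm to the stated objective. Under nesting the planned test has about 99% power at the 20-point target, so the claim of sufficient power survives, and an oversized standard error does not create a false claim of benefit. This stands, and it limits the severity. The 10-point and 15-of-83 examples concern effects smaller than the one targeted. The true-positive example is different: there a test that is too insensitive is not a safe error, because it can hide lost cancers.

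A second reply is that a χ² test in the analysis sentence could include McNemar's. The wording allows it. The sizing sentence does not, since it names Pearson and its 128 reproduces only for independent groups.

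A third reply is that every magnitude here assumes a denominator of 128 for both tests. This also stands. The Introduction's 85% and 40% are false-positive rates among biopsied men by Likert score, and 0.45 could likewise mean the share of index positives without significant cancer. With all 45 cancers kept, that denominator would be about 45/0.55 ≈ 81 rather than 128. The figures in steps 2 to 6 and step 8 would then not apply, although the two proportions would still come from the same men.

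A reader might infer from the 62.6% figure that the study is underpowered. The documents do not support this: that figure needs 64 separate men per test, and the study has no such groups. A reader might also infer that a planned confidence interval is wrong. The article plans no interval for the difference; the half-widths above are only those implied by the test's standard error.

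**Conclusion.** The point holds in a limited form. The article states a power and a test for two independent groups, while its own design gives paired, nested results on about 128 men. The stated 90% is not the power of this comparison, and an unpaired chi-square uses a standard error about 1.7 times too large at the planned effect. Counted over the same 128 men, the error is conservative: about 99% power at 20 points, about 22% at 10 points, and possible masking of a 31% loss of significant cancers. These sizes rest on three assumptions: a common denominator of 128, one classification per man, and nesting as the Data analysis section describes. That the sizing formula does not match the design needs none of them. This should be fixed. It does not threaten the study's ability to detect its planned effect.

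**What to change.** 1. Replace the unpaired chi-square with a paired analysis for each index test. Make the main result the paired difference in false positives, or the share of mpMRI false positives removed, with a 95% CI. Always report beside it the share of significant cancers retained, with its CI. Do not make McNemar's p-value the main evidence, for the reason in step 7.
2. State the denominator of the false-positive proportion: all Likert 3/4 biopsied men, or index positives only. If index positives only, use a paired method for predictive values instead.
3. Restate the sample-size paragraph. Say that 128 at 90% power is a per-group figure for independent groups and does not apply, and give the expected precision of the paired estimates at about 128 men (for example 31%, 22% to 42%, for false positives removed).

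The cost is rewording of the statistical section and a short recalculation. Recruitment, scanning and data collection stay as they are.
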